#### Assignment of interventions

Assessments will be performed by blinded investigators in a pseudonymized manner to ensure blind data collection and analysis. To avoid performance bias, measurements and interventions will follow a standardized protocol. The participating nursing homes (clusters) will be randomly assigned to the interventions by the project staff in the agreed order. The sports scientist or physiotherapist delivering the intervention will only receive the names of the participants in the intervention group without being aware of the design.

#### Outcome measures

The assessments focus on two key domains (primary outcomes) to evaluate the efficacy of the interventions (see Table 1): physical activitiy and physical functioning. Further assessments (secondary outcomes) evaluate physical and subjective performance measures, activities of daily living, cognition, psychological wellbeing and emotions, intention to be physically active, and stage of change. All measurements are listed in the SPIRIT diagram in Table 1.

**TABLE 1 T1:** Spirit diagram - Schedule of activities.

			Study period					
			Enrollment	Allocation	Baseline	Posttests		Follow-up
TIMEPOINT			*-t* _ *1* _	*t* _ *0* _	*t* _ *1* _	*t* _ *2* _	*t* _ *3* _	*t* _ *4* _
Enrollment	**Eligibility screen**		X					
	**Informed consent**		X					
	**Allocation**			X				
Intervention	Physical activity culture							
	Physical exercise intervention							
	Guided environmental intervention							
	Non-guided environmental intervention							
Assessments	*Primary Outcomes*							
	PA	Steps per day			X	X	X	X
	PF	SPPB			X	X	X	X
	*Secondary Outcomes*							
	PP	Hand grip strength			X	X	X	X
		Frailty			X	X	X	X
		Gait patterns			X	X	X	X
		Posture			X	X	X	X
	ADL	Barthel Index			X	X	X	X
		NNA			X	X	X	
		NHLSD			X	X	X	X
	COG	MoCA			X	X	X	
		Auditory Task			X	X	X	X
		Gait patterns DT			X	X	X	X
		Posture DT			X	X	X	X
		LMR			X	X	X	X
	HB	Subjective age			X	X	X	
		Subjective health			X	X	X	X
		Short-FES-I			X	X	X	
		PSC scale			X	X	X	X
	PWB	DIA-S			X	X	X	
		CES-D			X	X	X	
		EQ-5D-3L			X	X	X	
		WHOQOL			X	X	X	X
	Int	Intention			X	X	X	

Note: X implementation of the assessment; the line with two dots represents the period of the intervention phase with starting and endpoint, t-1 before pretest, t1 pretest, t2 and t3 posttests, and t4 follow-up. I1, Intervention 1; I2, Intervention 2; PA, Physical activity; PF, Physical functioning; PP, Physical performance measures, Frailty Fried Index; ADL, Activities of daily living; COG, Cognition; HB, Health behavior; PWB, Psychological well-being and emotions; Int, Intention; SPPB, Short Physical Performance Battery; NAA, Nuernberg-Ageing-Everyday-Life Test; NHLSD, Nursing Home Life Space Diameter; MoCA, Montreal Cognitive Assessment; LMR, Landmark Recognition Task; PSC scale, Psychological Self-Concept Scale; DIA-S, Depression in Age Scale; CES-D, Center for Epidemiological Studies Depression Scale; EQ-5D-3L, European Quality of Life; WHOQOL, World Health Organization’s Quality of Life, Intention Intention to be physically active and stage of change.

#### Screening

*Demographics.* Demographic characteristics will be assessed to describe the sample, including age (years), body height (m), body mass (kg), and body mass index (BMI). Additionally, we will screen for sex, leg length (relevant for the GAITRite gait analysis system), education, objective health (diseases and medications), COVID-19 infections, and use of assistive aids.

*Number of falls.* The nursing staff will have documented the number of falls occurring within the last 4 months.

### Primary outcomes

#### Physical activity (PA)

The *Fitbit Zip* (Fitbit, San Francisco, United States) device will be used to objectively track PA, and its 6-month battery life supports prolonged use. The Fitbit Zip has been validated for use in different age groups and conditions (Tully et al., 2014; Sharp et al., 2017; Streber et al., 2017), and it has been shown to deliver data that is considerably more accurate than subjective measures and close to that of the “gold standard” ActiGraph (Meyer et al., 2019). The Fitbit will be attached to participants’ clothes and will record their steps taken and distance traveled, which can be viewed on the Fitbit’s display. Participants will be instructed to wear the Fitbit Zip as often as possible throughout the project duration (52 weeks), immediately after waking up, and to remove it before going to bed. The data will be synced weekly; malfunctioning devices will be replaced (Tully et al., 2014; Sharp et al., 2017; Streber et al., 2017). To analyze steps per day, hours with at least one step will be identified as wearing hours (Meyer et al., 2016). Days with less than 6 h (identified as less than 6 h with at least one step) or not fulfilling the “three-a-day” criterion (using the tracker at least once in the morning, once around noon, and once in the afternoon, identified as at least one step having been registered) will be excluded from PA calculations. These days will be classified as non-wearing days, according to the heuristic of Meyer and colleagues (Meyer et al., 2017). Sedentary minutes will be defined as periods of at least 20 min with three or fewer steps per minute (Meyer et al., 2019). To calculate sedentary time and the *longest zero* time, we will exclude data from days with less than 6 hours of wearing. To express sedentary minutes as a percentage of total waking time, waking time will be defined as a 12-h period (Alessi et al., 2005). This definition of waking time is necessary because it is difficult to distinguish between non-wearing time and sedentary time (Meyer et al., 2017). Usage behavior will be quantified as the proportion of days worn.

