### Trial design

Based on existing research and the physical exercise recommendations mentioned above, this monocentric intervention study is conducted through a controlled cluster-randomized crossover design with four arms. The four interventions are randomly paired and ordered using MATLAB (‘nchoosek’ and ‘randperm’ functions), ensuring that each intervention will be combined with each of the other three interventions once. These six different intervention combinations were then clustered randomized to the nursing homes in the agreed order. In general, the trial design can be divided into an intervention and a follow-up phase with four separate weeks of measurements (t1-t4). So t1 is the baseline measurement time point, t2, with a double role, corresponds to the post-measurement point for the first intervention as well as the pre-measurement point for the second intervention phase. According to this, t3 will be the post-measurement point for the second intervention. 16 weeks after t3, the study will be concluded with the follow-up measurements (t4) after 52 weeks (see Figure 1). The date of first enrollment was August 2022.

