### Sample size estimate/power calculations

Statistical power analysis was conducted to estimate the sample size to test our hypothesis in G*Power (Version 3.1.9.4, Heinrich Heine University of Duesseldorf) (Faul et al., 2009). The following input parameters were used to obtain small-sized test × group interaction effects within an ANOVA: effect size (*f* = 0.15) (i.e., a small effect, (Tudor-Locke et al., 2011), type I error (α = 0.025), type II error (1-β = 0.8), number of groups (n = 4), number of measurements (n = 2), correlation between measurements (r = 0.60).

The size of the estimated sample to generate sufficient power to achieve the small effect is N = 88. To compensate for the estimated dropout rate of 30% (e.g., 20% lost to follow-up; plus 10% mortality) we plan to include a total of N = 116 participants. Based on the study design, we will integrate N = 29 participants in each condition.

Regarding the special cohort, recruiting approximately 30 participants per intervention arm per nursing home seems unrealistic, so multiple nursing homes will be needed for each intervention arm. As the number of nursing homes is also limited, each one needs to take on more than one intervention arm to reach a total of ∼30 participants. By the life expectancy of the special cohort and for ethical reasons, we have limited the maximum study duration to 1 year per participant. This means that each participant can complete two intervention phases and one follow-up phase per year, nested in a nursing home. In terms of the four intervention arms, this means six different possible combinations (this means six different nursing homes), each with 10–20 nursing home residents participating in the study.

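### Baseline steps may carry a first-week reaction to a readable tracker; this would enter phase-1 changes only, and the arms cannot share phase 1 equally

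*Protocol article*

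**What the plan says.** Under Physical activity (PA), the tracker is clipped to clothing and records "steps taken and distance traveled, which can be viewed on the" device's screen. Residents are asked to "wear the Fitbit Zip as often as possible throughout the project duration (52 weeks"). The same section says which days count: a day needs six hours with steps and some activity in the morning, around noon and in the afternoon. Neither rule concerns the first days of wear.

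Under Trial design there are "four separate weeks of measurements (t1-t4"). The article states: "So t1 is the baseline measurement time point". For the second phase, "t2, with a double role, corresponds to the post-measurement point for the first intervention as well as the pre-measurement point". At the end, "the study will be concluded with the follow-up measurements (t4) after 52 weeks". Interventions are paired at random, "ensuring that each intervention will be combined with each of the other three interventions once", and the order is also randomised.

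Under Statistical analysis, the steps model is a 4 (group) by 2 (time) linear mixed model, with the time factor written as t1:t2 and t2:t3. The follow-up model has three levels: t1/t2, t2/t3 and t4. No term is called a period or sequence effect.

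**The concern.** A resident who has just been given a device with a readable count may walk more than usual for a few days, or may record fewer steps while learning to wear it. Either way, t1 would differ from the resident's habitual level. By t2 the same resident has had the device for a full 16-week phase. The phase-1 change would then contain the fading of that reaction and the phase-2 change would not.

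If t1 is raised, whatever a home receives first looks less effective; if t1 is lowered, it looks more effective. This becomes a bias between arms when the arms differ in how often they come first. The trial plans for a small effect (f = 0.15), so a modest artefact could matter. The limitations paragraph in the Discussion covers non-wear, the lack of a traditional control group and adherence, but not reactivity to the tracker.

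**Working it through.** **1. When wear starts.** The Abstract gives 36 weeks for the two phases including measurement weeks, followed by 16 weeks: 36 + 16 = 52. Trial design places t4 after 52 weeks, and wear is set at 52 weeks. Wear therefore starts at about t1. This is an inference, since no issue date is stated.

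**2. Where a first-week shift goes.** Let d be the amount by which t1 steps exceed the habitual level, with the excess gone by t2.
- Phase-1 change (t2 minus t1): shifted by −d.
- Phase-2 change (t3 minus t2): no shift.
- Follow-up model: the pooled t1/t2 pre-level is raised by d in phase-1 homes only.

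**3. Bias in a contrast.** With six pairs used once each, every arm sits in three homes. If arm A comes first in k_A of its three homes, its mean change is shifted by −d × k_A/3. For A versus B, with equal home sizes and no period term:

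bias = −d × (k_A − k_B)/3

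**4. Can the arms be balanced?** There are six phase-1 slots for four arms, 6/4 = 1.5 each, so equal counts are impossible. Enumerating all 2^6 = 64 orders:

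| Phase-1 counts of the four arms | Orders |
|---|---|
| 3, 2, 1, 0 | 24 |
| 2, 2, 1, 1 | 24 |
| 3, 1, 1, 1 | 8 |
| 2, 2, 2, 0 | 8 |

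The four hypothesised contrasts are combined versus exercise, combined versus guided, exercise versus non-guided, and guided versus non-guided.
- Contrasts with unequal counts: two of the four in 32 orders, all four in 32, never fewer than two.
- Largest difference among the four: one home in 24 orders, two in 24, three in 16.
- A single contrast: difference 0 in 16 orders, 1 in 28, 2 in 16, 3 in 4. Mean absolute bias = d × (28×1 + 16×2 + 4×3)/(64×3) = d × 72/192 = 0.375d.

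**5. Size in steps.** The article gives no value for d. Assuming 5-20% of baseline steps:

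| d | d/3 | mean over orders, 0.375d | worst case, d |
|---|---|---|---|
| 5% | 1.7% | 1.9% | 5% |
| 20% | 6.7% | 7.5% | 20% |

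**6. Size against the design effect.** From the sample-size section, f = 0.15 and r = 0.60. In units of the SD of steps, the SD of a change is √(2 × 0.40) = 0.894. The corresponding f for changes is √(0.15² × 2/0.40) = 0.335. The planned SD between arm mean changes is 0.335 × 0.894 = 0.30. The table sets the spurious SD between arms beside it, with the rejection rate of a simple four-group change-score ANOVA at N = 88 and nominal level 0.025.

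| Assumed shift | Spurious SD between arms | Share of 0.30 | Rejection rate |
|---|---|---|---|
| 0.1 SD | 0.017-0.037 | 6-12% | 0.026-0.030 |
| 0.3 SD | 0.050-0.112 | 17-37% | 0.035-0.083 |

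Ranges run over the four patterns in step 4. The ANOVA ignores clustering and is only a yardstick.

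**The case against.** **Nothing shows a reaction.** A reader might infer that t1 is a novelty reading and that baseline is too high. No passage says that residents respond to the screen, in which direction or for how long. The eligibility criteria admit wheelchair users, and early wearing problems could lower the count. This stands: d is an assumption in both size and sign. If it were positive, the Discussion's expectation that follow-up values stay above baseline would become harder to confirm, not easier.

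**The start of wear is inferred.** The 36 weeks contain 32 of intervention, which leaves four for t1 to t3, so the t1 window could be longer than a few days. An article may also omit operational detail. This stands in part. However, the article does set out its day-exclusion rules, and the 52 weeks leave no visible room for wear before t1.

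**Distortion in every comparison.** A reader might infer that it can never cancel between arms. Any one contrast has matching counts, and so no bias, in 16 of 64 orders. Random order also makes the expected bias zero. What remains is that one order was drawn, it is not reported, and at least two of the four hypothesised contrasts are unequal in it.

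**The model may handle it.** If t1:t2 and t2:t3 denote the two phases, the factor acts as a period effect and absorbs an additive shift, leaving zero bias. The follow-up notation, which pools t1 with t2 and t2 with t3, suggests pre and post instead. The wording is ambiguous. Conditional baseline adjustment would not reliably help, because the shift lies in the pre-value itself.

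**Any period effect does this.** True: season or general decline gives the same pattern, which adds to the case for a stated period term.

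**Conclusion.** The concern holds as a risk, not as a demonstrated bias. The readable count, t1 as the pre-value of phase 1 only, and unequal phase-1 exposure are stated or follow by arithmetic. Wear beginning at t1 is a sound inference; the reaction itself is assumed.

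If it exists and fades by t2, an affected contrast is biased by d/3 to d and a matched one by zero. The consequence is negligible for a shift near 0.1 SD and material from about 0.3 SD. These figures assume equal home sizes, whereas the plan expects six homes, "each with 10–20 nursing home residents participating in the study"; unequal sizes can add to the imbalance. They also assume no period term and a shift that is the same in all arms. Only the steps outcome is touched; the SPPB is not. The point is worth acting on because the remedy is cheap and protects a primary outcome.

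**What to change.** - **Analysis, all homes.** State an explicit period effect (phase 1 versus phase 2) in the steps model. It can always be estimated here. It would be confounded with the arms only if one set of arm values gave a difference of 1 between the first and second intervention in all six homes. Among any three arms that is impossible: if A precedes B and B precedes C, A and C differ by 2, not by 1 or −1.
- **Homes already measured.** Add a sensitivity analysis that drops the first days of wear and takes baseline steps from the later days of the t1 window, before the intervention begins. The weekly synced records should also show whether counts drift during those days.
- **Homes not yet started, if any.** Issue the tracker about one to two weeks before t1 and take baseline steps after the first 7 days of wear. Enrolment began in August 2022 and home recruitment ended in the third quarter of 2023, so this may apply to few or none.
- **Reporting.** Give the realised order and each arm's phase-1 count, and list tracker reactivity among the limitations.

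The cost is slightly longer wear, within the stated six-month battery life of the device, a little discarded data and one model term. Covering the screen is debatable and is not needed for this remedy.

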**Methods:**

The study employs a cluster-randomized controlled crossover design with four intervention groups. Participants will be randomly assigned to one of four groups: a combined exercise and guided environmental intervention (physical activity-promoting culture), an exercise intervention, a guided environmental intervention, or a non-guided environmental intervention. The exercise intervention involves group-based sessions twice a week, while the environmental intervention focuses on implementing PA into daily routines. The guided environmental intervention is equivalent to the non-guided one but provides additional support two to four times weekly. We aim to recruit at least 120 participants from six nursing homes. Each facility will receive two interventions in a 16-week crossover design (36 weeks in total, including weeks for measurements), followed by a 16-week non-guided environmental intervention (follow-up phase). Primary outcomes include steps per day as an indicator of PA behavior, and the Short Physical Performance Battery (SPPB) to assess physical functioning.

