Physical and cognitive abilities as well as psychosocial well-being can be maintained or improved even in older adults suffering from multiple health problems by appropriate interventions such as physical exercise (Mulrow et al., 1994; Kryger and Andersen, 2007; Pedersen and Saltin, 2015; Cordes et al., 2021a). However, the type, design, and duration of the training must be considered to achieve training effects. For example, interventions that combine cognitive and physical exercise components tend to more strongly benefit both motor and cognitive performance than interventions focused on pure motor or cognitive training (Wollesen and Voelcker-Rehage, 2014). Combined physical and cognitive training interventions have been shown to improve physical abilities, including physical strength, cardiorespiratory fitness, flexibility, balance, and everyday functionality and mobility (Fiatarone et al., 1990; Sherrington et al., 2008; Liu and Latham, 2009; Marmeleira et al., 2009; Gine-Garriga et al., 2010; Matsuda et al., 2010; Steib et al., 2010). Furthermore, these interventions have been demonstrated to reduce falls and physical frailty. They also seem to benefit cognitive functions (Marmeleira et al., 2009), including visual attention, executive functioning, and speed of information processing. With respect to the design, duration, and frequency, intervention studies that adapt to individuals’ abilities, focus on personal resources and are conducted twice a week for 45–60 min have been found to have the most positive effects (Wollesen and Voelcker-Rehage, 2014; Cordes et al., 2021a).

Beyond exercise interventions, promoting daily physical activity (PA) in nursing homes seems to be an urgent issue, as nursing home residents do not get sufficient PA in their normal lives. For example, Auerswald et al. (2022) investigated the PA behavior of nursing home residents using activity trackers (Fitbit Zip). On average, nursing home residents took 1.020 steps per week (–600 m) and spent 9 h per day sitting or lying down. At least two and a half of these hours were spent sitting or lying down continuously (see (Clark and Sugiyama, 2015; Vallance et al., 2018) for similar results). These findings indicate that the daily lives of nursing home residents lack PA, which can harm their health. Research has shown that there is a correlation between the amount of time spent sitting and the risk of mortality (Ebeling et al., 2013; Ministry of Health, 2013).

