#### Eligibility criteria

Inclusion criteria are: (i) voluntary participation, (ii) ability to participate in group training, (iii) minimum age of 60 years, (iv) ability to understand and implement instructions given by a trainer, and (v) ability to sit freely in a (wheel)chair. No other criteria are applied. If a study participant no longer fulfills the inclusion criteria due to a natural, age-related deterioration in general condition, they will be excluded from study participation (but they will be welcome to continue participating in the interventions voluntarily).

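### The valid-day rule infers wear from recorded steps, so steps per day is selected on its own value and residents who rarely or never step become missing rather than low

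*Protocol article*

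**What the plan says.** The abstract names the outcome: "Primary outcomes include steps per day as an indicator of PA behavior". Under Primary outcomes, Physical activity (PA), "hours with at least one step will be identified as wearing hours". A day must pass two tests. The first is six such hours; the days that fail it are given as "Days with less than 6 h (identified as less than 6 h with at least one step"). The second is a recorded step "once in the morning, once around noon, and once in the afternoon" (the three-a-day criterion). Days that fail either test "will be excluded from PA calculations" and are labelled non-wearing days; the rule is credited to a published heuristic. No measure of wear other than steps enters it. The same section explains its 12-hour definition of waking time by saying that "it is difficult to distinguish between non-wearing time and sedentary time".

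Three other places matter:

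- Eligibility criteria require "v) ability to sit freely in a (wheel)chair" and set no walking criterion.
- Statistical analysis handles missing data by multiple imputation under a missing-at-random assumption.
- The limitations paragraph of the Discussion says that zero-step periods may be non-wear and that incomplete wear may lead to underestimation. It does not mention loss of worn, low-activity days.

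**The concern.** Wear status should be established separately from the outcome. Here it is a function of the outcome. A resident who wears the tracker all day but walks in only four separate hours contributes nothing, while the same resident on a busier day contributes a full value. The average is taken over the busier days, and the selection is strongest for the least active residents, whom the trial most wants to move.

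Two things are at stake. First, the arms work through different routes. The environmental interventions aim to spread activity through the day, whereas the exercise intervention adds scheduled sessions. A rule that treats more active hours differently from more steps within an hour may not treat these arms alike, and they are the arms the hypotheses compare. Second, a resident who takes no steps has no valid day at all. A value that is in truth near zero becomes missing, and it is missing because it is low, which is the situation that missing-at-random imputation assumes away.

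**Working it through.** The article gives no expected share of valid days and no number of non-walking residents, so there is no figure of its own to reproduce. The rule was applied as written to days that are fully worn, so every rejected day is a false non-wear day.

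**Inputs from the article:** 12 waking hours; six step-hours per valid day; three-a-day. **Assumptions, not from the article:** full wear; each hour contains a step with probability p, independently; constant steps per active hour.

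**Step 1. Six-hour rule.** Active hours X ~ Binomial(12, p). The true mean is 12p, the share kept is P(X ≥ 6), and the observed mean is E[X | X ≥ 6].

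| p | True mean active hours | Worn days kept | Mean on kept days |
|---|---|---|---|
| 0.3 | 3.6 | 0.118 | 6.42 |
| 0.4 | 4.8 | 0.335 | 6.70 |
| 0.5 | 6.0 | 0.613 | 7.10 |

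- From p = 0.3 to 0.4: true gain 4.8/3.6 = 1.33, observed 6.70/6.42 = 1.04.
- From p = 0.4 to 0.5: true gain 6.0/4.8 = 1.25, observed 7.10/6.70 = 1.06.

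Adding three-a-day (three blocks of four hours, at least one active hour in each, at least six in total) changes little: 11%, 32% and 59% of worn days are kept.

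**Step 2. The other kind of gain.** Hold p = 0.4 and raise steps per active hour by 20%. The relative gain is 20% with or without the filter. In units of one active hour's steps, the absolute gain is 0.2 × 4.8 = 0.96 in truth and 0.2 × 6.70 = 1.34 on kept days. It is preserved in relative terms and inflated in absolute terms.

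**Step 3. Simulation of both tests together.** Assumptions: walking bouts Poisson and evenly spread over 12 hours, 50 steps per bout, full wear.

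| Bouts per day | Days kept | True steps/day | Observed steps/day |
|---|---|---|---|
| 2 | 0.5% | 100 | 334 |
| 4 | 9% | 200 | 376 |
| 6 | 30% | 300 | 426 |
| 8 | 55% | 400 | 485 |
| 12 | 87% | 600 | 631 |
| 20 | 99% | 1001 | 1003 |

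- Two more bouts per day (true gain about 100 steps) show as 50 from 4 to 6 bouts, 58 from 6 to 8, 69 from 8 to 10 and 86 from 12 to 14.
- At 6 bouts per day, 20% more steps per bout is a true gain of 60 that shows as 85. Two 500-step sessions a week are a true gain of 143 that shows as 170.

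The size depends heavily on baseline activity. The Introduction prints a background figure of 1,020 steps per week, or 1,020/7 ≈ 146 per day. That is about three bouts here, with well under 10% of worn days kept. At around 1,000 steps per day the rule would be almost harmless (99% kept).

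**Step 4. Residents with no valid day.** For someone who takes no steps this is certain, by definition. In a simulated mixed cohort (gamma spread with shape 1.5, averaging 5, 8 or 12 bouts per day), 25%, 15% and 9% of residents have no valid day in 112 fully worn days (16 weeks × 7).

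**Step 5. Three-a-day alone.** With three four-hour blocks, the share kept is [1 − (1 − p)^4]^3 = 44%, 66% and 82%. The mean on kept days is 12p/[1 − (1 − p)^4] = 4.74, 5.52 and 6.40. The gains show as 5.52/4.74 = 1.16 and 6.40/5.52 = 1.16. Selection is reduced but not removed.

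**The case against.** A tracker without a wear sensor needs some wear rule, and every such rule trades one error for another. This one is fixed in advance, rests on a cited heuristic, and is accompanied by a report of the proportion of days worn and an admission that non-wear and sitting are hard to separate. All of that is fair, and it is a reason not to insist on replacing the rule. It does not alter the fact that validity depends on the outcome.

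Three stronger readings are tempting, and the documents support none of them.

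- A reader might infer that steps per day is overestimated in every arm. That assumes full wear. Residents are asked to wear the device as often as they can, and unworn hours on a kept day count as zero steps, a downward bias that the limitations paragraph names. The net sign is not given.
- A reader might infer that differences between arms shrink towards zero. Steps 2 and 3 show that this holds for gains in active hours only. Three of the four interventions include scheduled sessions, and gains of that kind can look larger.
- A reader might take the background remark that residents "spent 9 h per day sitting or lying down" to mean that most worn days fail. One step makes a wearing hour, so nine hours of sitting or lying are not nine step-free hours.

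The wheelchair point also has limits. The number of residents who never step is not stated, those who walk for part of the day may have valid days, and the imputation model is not described. A relaxed rule is itself step-based and admits part-worn days.

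**Conclusion.** The concern holds in a limited form. From the text alone, worn days with fewer than six step-hours are deleted as non-wear, so a primary outcome is selected on its own value, most strongly for the least active. Gains that come as more active hours are compressed. Gains from more steps per active hour or from scheduled sessions are preserved, or inflated in absolute steps. The rule can therefore distort comparisons between arms, in a direction that the article does not determine.

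Also from the text alone, a resident who takes no steps has no valid day, and eligibility does not exclude such residents. Their missingness depends on the unobserved low value, which the missing-at-random assumption does not allow for.

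The sizes (12% to 61% of worn days kept; true gains of 33% and 25% shown as 4% and 6%) are illustrative. They rest on assumed full wear, independent hours and constant steps per active hour, and they fade as baseline activity rises. This should be dealt with before analysis, but it does not invalidate the outcome.

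**What to change.** 1. For residents documented as unable to walk at an assessment, enter 0 steps per day for that assessment instead of imputing. State the documentation that will be used, for example the SPPB gait component together with recorded wheelchair use.
2. The cited six-hour rule may stay as the main definition. Pre-specify a sensitivity analysis of steps per day with three-a-day alone, and say that it too is step-based and only reduces the selection.
3. Pre-specify a missing-not-at-random sensitivity analysis for residents with no valid days.
4. Report the share of valid days by intervention and period.
5. Add to the limitations that the rule can overestimate activity as well as underestimate it.

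The cost is small: a re-derivation from the hourly step data that the rule already needs, and two further analyses. The downside is that the relaxed rule keeps some part-worn days, which adds noise and some downward bias to that sensitivity analysis.
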